### Sample size

Following preliminary planning, we followed the DELTA^2^ guideline to estimate the minimum sample size for the study [27]. Frederick and VanderWeele’s meta-analysis [7] was used to specify the important and realistic target difference for the primary outcome, with an estimate of its uncertainty. A sensitivity calculation was included if assumptions are mis-specified.

For comparison to the duration of the IPS intervention in IPS-AD, we used the rate of competitive employment status reported by seven superiority trials which evaluated 12 months of IPS (928 participants; outcome rate 0.36 for IPS and 0.13 for TAU; odds ratio (OR) 3.76; 95% CI 2.70 to 5.24). Conservatively, we used the lower bound of the CI (i.e. 2.70; equivalent to an outcome rate of IPS 0.36 and TAU 0.18).

To achieve 90% power to detect this 18% target difference (with a two-sided 5% level of statistical significance and a 20% increase to compensate for missing or inaccurate NINO information) we estimate that 302 participants will be required with AUD and OUD (giving an expected 95% CI estimate for the OR effect within a range from 1.50 to 4.36). If the observed effect falls short of the target difference, we will be able to detect a 15% difference (which we judge is still important) with 83% power (OR 95%, CI 1.24–3.46).

Given the lower number of people in treatment with other drug use disorders, we expect to recruit fewer participants in this group, so it will be realistic to power the analysis at 80%. For the 18% target difference (two-sided, 5% level of significance and with 20% increase for attrition), 228 participants will be needed (95% CI 1.35–4.57).

For the secondary outcome of total time worked, four of the seven trials used for the power calculation for the primary outcome measure in the meta-analysis reported the total number of hours worked (i.e. the sum of all time in all competitive employment during the trial). These four trials recruited 376 participants and the pooled mean difference was 505 h (Hedges’ *g* effect size = 0.54; 95% CI 0.33–0.74). Using this effect size as the realistic mean target difference, the analysis of the secondary outcome for length of competitive employment will have 99% to detect this target difference for the AUD and OUD groups. For the other drug use disorder group, we will be able to detect an effect size ranging from 0.54 to 0.38 with a minimum of 82% power.

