With these conservative planning assumptions, a total of 832 participants will be the minimum number of participants required. Mediation analysis and longer-term follow-ups will benefit from a greater sample size, so recruitment is expected to extend well beyond this minimum.

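### Subgroup power for total time worked rests on an uncut effect (g = 0.54) while the primary effect was cut to its lower confidence limit, and the 82% for other drug use disorder ignores the allowance for attrition

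*Protocol article*

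**What the plan says.** All of this is in the Sample size section of the protocol article.

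- **Primary outcome.** Seven trials gave 0.36 v 0.13, OR 3.76 (95% CI 2.70 to 5.24). The plan does not use 3.76: "Conservatively, we used the lower bound of the CI (i.e. 2.70; equivalent to an outcome rate of IPS 0.36 and TAU 0.18". With a 20% increase this leads to 302 participants in each of AUD and OUD (90% power) and 228 in other drug use disorder (80% power), 832 in all.
- **Total time worked.** Four of those seven trials supply the effect: "These four trials recruited 376 participants and the pooled mean difference was 505 h (Hedges" g "effect size = 0.54; 95% CI 0.33–0.74"). Here the point estimate is used as it stands: "Using this effect size as the realistic mean target difference, the analysis of the secondary outcome for length of competitive employment will have 99" per cent power in the AUD and OUD groups.
- **Other drug use disorder.** For this group, "we will be able to detect an effect size ranging from 0.54 to 0.38 with a minimum of 82% power".
- **Closing sentence.** The total of 832 is introduced by the words "With these conservative planning assumptions".

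The section on analysis of secondary outcomes describes the separate models for the three diagnosis groups as exploratory.

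**The concern.** Two effects from overlapping trials are treated differently in the same section. The employment effect is cut to its lower confidence limit. The effect on time worked, which depends on employment because anyone who never works contributes zero, is not cut. A reader who has just seen the cautious step for the primary outcome will take 99% to be equally cautious. The two targets also fit together only under an assumption about time worked per employed person, which the section does not state.

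The power for other drug use disorder has a further problem. The 228 is stated to include a 20% increase for attrition, so a power quoted as a minimum should hold on the number left after that loss.

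What is at stake is how a null result for time worked in one diagnosis group is read. A 99% figure suggests a 1% chance of missing the effect. At the lower confidence limit that chance is about 26% in AUD or OUD on the net number.

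**Working it through.** **Inputs from the Sample size section.** Two-sided 5%; g = 0.54, CI 0.33 to 0.74; lowest effect quoted for other drug use disorder 0.38; 302, 302 and 228 participants; 20% increase. Allocation 1:1 is from the Procedure section. Net numbers: 302/1.2 = 252, 228/1.2 = 190, 832/1.2 = 693.

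**Formula.** For total N split equally, power ≈ Φ(g·√(N/4) − 1.96). The noncentral t gives nearly the same. This is a simple two-group comparison of means, used as an approximation to the planned mixed model.

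**Step 1: reproduce the plan's figures.**

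- AUD or OUD, g = 0.54, N = 252: 0.54 × √63 = 4.286; less 1.96 = 2.326; power 99.0%. With N = 302 it is 99.7%. The stated 99% is confirmed, and it holds on the net number.
- Other drug use disorder, g = 0.38, N = 228: 0.38 × √57 = 2.869; less 1.96 = 0.909; power 81.8% (noncentral t 81.5%). The stated 82% is confirmed, but only with all 228.
- Same effect, N = 190: 0.38 × √47.5 = 2.619; less 1.96 = 0.659; power 74.5% (noncentral t 74.1%).

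So the 99% survives the 20% allowance and the 82% does not.

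**Step 2: apply the primary outcome's rule (lower limit, g = 0.33).** Noncentral t:

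| Group | Net of the 20% increase | All recruited |
|---|---|---|
| AUD, and likewise OUD | 74% (252) | 82% (302) |
| Other drug use disorder | 62% (190) | 70% (228) |
| All diagnoses pooled | 99.1% (693) | 99.7% (832) |

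This step needs nothing beyond the interval printed in the article.

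**Step 3: does g = 0.54 fit 0.36 v 0.18?** Let mean time among workers be 1 under IPS and r under TAU, with coefficient of variation c among workers in both arms. Non-workers count as zero. Then

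g = (p1 − p0·r) / √{½[p1(1+c²) − p1² + r²p0(1+c²) − (p0·r)²]}, with p1 = 0.36 and p0 = 0.18.

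The article gives neither r nor c, so both are assumptions, shown over a range:

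- Equal time per worker (r = 1): g = 0.414 at c = 0, 0.397 at c = 0.25, 0.355 at c = 0.5, 0.266 at c = 1.
- c = 0.25, r = 0.75 (IPS workers work 1/0.75 = 1.33 times as long): numerator 0.36 − 0.135 = 0.225; arm variances 0.2529 and 0.0894, mean 0.1711, square root 0.4137; g = 0.544.
- c = 0.5: g = 0.54 needs a ratio of about 1.5.
- c = 1: it needs a ratio of about 3.

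The effect of 0.54 is therefore compatible with the planning rates, but only if employed IPS participants work substantially longer than employed TAU participants.

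**Step 4: is the cut to 0.18 the cause of the gap?** With the uncut rates 0.36 v 0.13 and equal time per worker, g = 0.555 at c = 0, 0.476 at c = 0.5 and 0.356 at c = 1. Even these rates reach 0.54 only when time varies little between workers, so the cut alone does not explain the gap.

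**The case against.** The strongest reply has four parts.

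1. **The arithmetic is right and the assumption is disclosed.** The 99% is correct for the stated effect, and the article prints the interval down to 0.33. Planning a secondary outcome on a point estimate is a legitimate choice. This stands, and the 99% should not be called a miscalculation.

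2. **The planning rates can produce 0.54.** A reader might infer that 0.36 v 0.18 rules out g = 0.54, since equal time per worker caps g at 0.41. The documents do not support that. They never say that workers in both arms work equally long. The Background section reports longer job tenure under IPS (d 0.55), and the intervention includes in-work support. What remains is that the needed difference, about 1.3 to 1.5 times at a coefficient of variation of 0.25 to 0.5, is not stated.

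3. **Much lower power figures are selective.** A reader might take the true power in AUD or OUD to be 56% to 64%, the value at g = 0.27. That rests on an assumed coefficient of variation of 1 and lies below the lower limits of both relevant intervals in the article: 0.33, and 0.35 for time worked in the 30-trial meta-analysis (d 0.46). This objection stands, and the scenario is not relied on here.

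4. **The consequence is small.** The hours effect set no sample size, and the sentence that speaks of conservative assumptions introduces a total derived from the primary outcome. The diagnosis-group models are exploratory, results carry 95% confidence intervals, and recruitment is expected to pass the minimum. All of this is fair and limits the weight of the point.

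None of it answers the different treatment of two effects from overlapping trials, or the 82% computed without the attrition allowance.

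**Conclusion.** The point holds as one of inconsistent planning inputs and one of inconsistent denominators. At the lower limit g = 0.33, the basis used for the primary outcome, power for total time worked is about 74% in AUD and in OUD and about 62% in other drug use disorder on net numbers (82% and 70% if nobody is lost). The pooled analysis keeps about 99%. The 82% at g = 0.38 for other drug use disorder is about 74% once the 20% allowance is used up.

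These figures assume a two-sided 5% comparison of two means, equal arms and net numbers of 252, 190 and 693. The statement about time per worker rests on assumed coefficients of variation. The point does not show that the trial is underpowered for its pooled analysis. Its importance is modest: published subgroup figures look firmer than the section's own cautious rule would make them.

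**What to change.** In the Sample size section:

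- Keep 99% and label it as the power at g = 0.54. Add the power at g = 0.33 on analysable numbers: about 74% in AUD and in OUD, about 62% in other drug use disorder, about 99% pooled.
- Restate the other drug use disorder figure at g = 0.38 as about 74%, or say that 82% assumes no attrition.
- If 0.54 remains the target, state that together with 0.36 v 0.18 it assumes that employed IPS participants work longer than employed TAU participants, and give the ratio assumed.

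The cost is a few sentences. Sample size and analysis stay as they are; the stated subgroup figures become less favourable. If the article can no longer be edited, the same figures can go into the SAP.

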### Study governance

Following signed terms of reference and charter respectively, an independently chaired Trial Steering Committee (TSC) and Data Monitoring Committee (DMC) will oversee study integrity, recruitment, research measure completion and analysis. These committees will include members with addiction service delivery, commissioning or IPS expertise, and patient and public involvement (PPI). The Trial Management Group will be responsible for day-to-day running of the study and members will attend meetings of the oversight committees. After approving the protocol, the TSC and DMC will meet approximately three times each year.

All serious adverse events will be promptly reported to the DMC (for the TSC) and the study sponsor. The chief investigator will have overall responsibility for the trial dataset, supported by the oversight committees. The study may be prematurely discontinued by the sponsor, or for reasons reported by the chair of the DMC to the chair of the TSC.

### Information governance and data linkage

Physical case report forms will be securely stored at each site. Sites will report research data and management information securely via NDTMS. A data submission portal will transfer monthly patient information to the study. Clinical site personnel will use a two-factor authentication before access to submit data.

A bespoke Local Data Collection System (LDCS) will collect data on participant identification characteristics, scheduled and attended IPS support sessions, and self-report job data to facilitate study monitoring. LDCS will be used by the principal investigator (PI) and ES at each site with data sent to the study via secure file transfer. All study data will be stored in password-protected folders within a restricted area of PHE’s network, accessible only by a limited number of authorised analysts. Additionally, there will be physical and other data-security safeguards to protect the data, and audit processes.

The planned deterministic data-linkage procedure (to be described in detail in the pre-registered analysis plan) will be based on the participant’s NINO for vocational outcomes, and NHS number for health-related outcomes. If the event of missing data, linkage will be done utilising the participant’s full first name and surname, date of birth, gender and full or partial postcode or upper-tier local authority of residence. The HES patient identifier will be used to verify that a participant has been linked to a single HES patient. Linkage with offending databases (PNC and p-NOMIS) will utilise a participant’s full first name and surname, date of birth, gender and upper-tier local authority of residence. Data to enable linkage will be transferred from PHE to government departments via a strong password-protected, encrypted, file-transfer protocol. This transfer and linkage protocol will be reviewed periodically and may be enhanced.

### Analysis

Descriptive analysis will summarise the sample in terms of demographic, clinical and vocational history characteristics. For those attaining competitive employment during the study, we will summarise their earnings and income using HMRC’s RTI system.

#### Primary vocational effectiveness

The statistical analysis plan (SAP) will be approved by the trial committees and will be published on the Open Science Framework (OSF; www.osf.io) before it is implemented after data-lock. There will be no interim analyses and specified trial-stopping rules. The analysis of the primary outcome (completed in STATA or R; final code to be placed on OSF) will follow the intention-to-treat (ITT) principle and include all patients in the group to which they are allocated. Alpha will be set at 5% for the primary and secondary outcomes (with associated 95% CIs). The distributions of scale and count measures may be non-normal (skewed), so that test statistics and effect sizes may be computed following appropriate transformation (e.g. natural log to obtain a geometric mean).

Data from all sites will be pooled and the superiority effectiveness estimate for the IPS intervention (adjusted OR and CI) will be determined using a mixed-effects, multi-variable logistic regression model. The model will include the stratification variables and a random intercept for each site to account for clustering. A maximum-likelihood multiple-imputation approach will be used for the management of missing data with a sensitivity comparison to the complete case dataset.

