### Study population and setting

Study populations will be adults, unemployed and economically inactive^2^ enrolled in community treatment for AUD, OUD or another drug use disorder. The minimum total target sample will be 832 participants. The plan is to include seven clinical recruitment sites in Birmingham, Blackpool, Brighton and Hove, Derbyshire, London Borough of Haringey, Sheffield and Staffordshire. Each site will be a NHS, not-for-profit, or private organisation providing community/outpatient treatment for alcohol and drug dependence. According to the treatment capacity of each site, two or more Employment specialists (ES) will deliver IPS.

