### Procedure

All keyworkers and ES will complete National Institute for Health Research’s Good Clinical Practice (GCP) training. Potential participants will be referred to an ES in the clinical team to discuss the study. The King’s College London Clinical Trials Unit will programme and independently manage the study randomisation system on a secure website. Immediately after securing informed consent (IPS-AD Participant Information Sheet (PIS) and Participant Consent Form (PCF) is available from the corresponding author on request) and completion of baseline study questionnaires, the ES will access the randomisation website to assign the participant to the intervention or control condition. Group allocation (ratio 1:1) will be done using block randomisation (with varying block size) stratified by site, clinical diagnosis (AUD, OUD, other drug use disorder) and work history (1 month or less versus more than 1 month of paid employment in the last 5 years).

The randomisation system will immediately confirm the participant’s allocation to IPS or TAU by email. The ES will then inform the participant and their keyworker. Participants assigned to TAU will be given an information pack containing details of standard employment support services available locally and will have no further contact with the ES. It will not be feasible to blind clinicians to trial condition allocation. Enrolment in TAU will be ongoing after the trial according to patient preference and local policy.

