### IPS intervention principles and delivery

IPS will be offered as an individual (one-to-one) intervention for 9 months with up to four additional months of in-work support if competitive employment is attained. IPS will be provided without restriction due to job readiness, work history, qualifications and homelessness status. In weekly sessions in the first month, the ES will: (1) discuss opportunities to work and will give advice on welfare benefits, including the availability of in-work benefits; (2) develop a vocational profile of the participant’s skills, experience and employment preferences; (3) help the participant to write or update their curriculum vitae/resumé; and (4) help the participant to implement a rapid job search. As appropriate, the ES will contact local employers and help the participant to complete job applications and prepare for interviews. The ES will seek to develop relationships with local employers and discuss opportunities to tailor work for people recovering from alcohol and drug dependence.

After the first month, IPS sessions will be scheduled approximately fortnightly, with additional phone and email contact provided as needed. Once the participant starts work, the ES will offer in-work support. This support will be approximately weekly contacts in the first month, then fortnightly. The ES will discuss how the participant is adapting to their new job; assist with any referral for medical treatment; and, with consent, seek to discuss job-flexibility issues with the employer (e.g. adjusting shift patterns to enable the participant to collect treatment medication from a retail pharmacy).

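### The primary model's only clustering term is site, so any differences between employment specialists, which act in the IPS arm alone, are left out of the standard error

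*Protocol article*

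**What the plan says.** Under Primary vocational effectiveness, the article pools all sites in a mixed-effects logistic regression that has the stratification variables and "a random intercept for each site to account for clustering". Randomisation is individual, 1:1, and "stratified by site, clinical diagnosis (AUD, OUD, other drug use disorder) and work history" (Procedure).

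The delivery of IPS is described elsewhere:

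- Study population and setting: "The plan is to include seven clinical recruitment sites", and at each of them "two or more Employment specialists (ES) will deliver IPS".
- IPS intervention principles and delivery: "IPS will be offered as an individual (one-to-one) intervention for 9 months". The ES builds the vocational profile, helps with the job search and applications, and cultivates local employers.
- Procedure: participants allocated to TAU "will have no further contact with the ES".

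The Sample size section has no design effect and gives no ICC.

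**The concern.** Because participants are randomised individually within site, a site effect is common to both arms and largely cancels from the IPS versus TAU comparison. Clustering that arises in one arm only does not cancel. All IPS participants of one ES share that person's skill and employer contacts, and these bear directly on whether someone gets a job. TAU participants have no such grouping. This is a partially nested design: clusters in the IPS arm, independent individuals in the control arm.

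A model whose only grouping is site treats the IPS participants of one site as independent given site. If ES within a site differ in their results, the variance in the IPS arm is understated. At stake are the coverage of the 95% confidence interval and the type I error of the primary test, in a trial whose Discussion promises a definitive estimate of effectiveness.

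**Working it through.** **1. The plan's own figure.** Inputs from Sample size: rates 0.36 and 0.18, two-sided 5%, 20% inflation. A two-proportion formula with pooled variance and no continuity correction gives 126 per arm at 90% power and 95 per arm at 80%. Then 252 × 1.2 = 302.4 and 190 × 1.2 = 228. Taking 302 for each of AUD and OUD, 302 + 302 + 228 = 832. The total is thus reproduced with no allowance for clustering.

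**2. Inputs for the check.** 832 / 2 = 416 per arm. Seven sites with at least two ES each give at least 14 ES. *Assumptions, not in the article:* up to 28 ES in total, equal caseloads, and a within-site ES ICC of 0.01 to 0.05 on the scale of the yes/no outcome.

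**3. Formulas.**
- Caseload m = 416 / (number of ES). IPS-arm design effect DE = 1 + (m − 1) × ICC.
- Arm variances: 0.36 × 0.64 = 0.2304 and 0.18 × 0.82 = 0.1476, sum 0.3780.
- True SE / model SE at the planned rates = √[(DE × 0.2304 + 0.1476) / 0.3780].
- Type I error applies under equal rates, so the ratio there is R = √[(DE + 1) / 2], and type I error = 2 × [1 − Φ(1.96 / R)].

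**4. Results.**

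| ES | m | ICC | DE | SE ratio, 0.36 v 0.18 | Model SE too small by | R under the null | Type I error |
|---|---|---|---|---|---|---|---|
| 14 | 29.7 | 0.01 | 1.29 | 1.08 | 8% | 1.07 | 6.7% |
| 14 | 29.7 | 0.02 | 1.57 | 1.16 | 14% | 1.14 | 8.4% |
| 14 | 29.7 | 0.05 | 2.44 | 1.37 | 27% | 1.31 | 13.5% |
| 20 | 20.8 | 0.02 | 1.40 | 1.11 | 10% | 1.09 | 7.3% |
| 28 | 14.9 | 0.01 | 1.14 | 1.04 | 4% | 1.03 | 5.8% |
| 28 | 14.9 | 0.02 | 1.28 | 1.08 | 7% | 1.07 | 6.6% |
| 28 | 14.9 | 0.05 | 1.69 | 1.19 | 16% | 1.16 | 9.1% |

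A ratio of 1.37 means that the model SE is 1 − 1/1.37 = 27% too small. At ICC 0, DE = 1 and every ratio is 1.

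**5. Power.** In the worst row, the correct SE of the risk difference is √[(2.44 × 0.2304 + 0.1476) / 416] = 0.0413. Power for 18 points is Φ(0.18 / 0.0413 − 1.96) = 99%. All other rows are higher.

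**6. Simulation.** Logistic data with seven sites, two ES per site, N = 832, no IPS effect conditional on ES, site fitted in the model, and the ICC set on the latent (logit) scale:

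| Latent ICC | Rejection at nominal 5% | Empirical SE / mean model SE |
|---|---|---|
| 0 | 4.9% | 1.00 |
| 0.01 | 5.9% | 1.05 |
| 0.02 | 5.7% | 1.06 |
| 0.05 | 10.9% | 0.213 / 0.181 = 1.18 |

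These values are lower than the formula's because a latent ICC is a smaller ICC on the yes/no scale. At a rate of 0.18, a latent ICC of 0.05 is roughly (0.05 / 0.95) × 3.29 × 0.1476 = 0.026. With 14 ES that gives DE = 1.73 and R = 1.17, in line with the simulated 1.18. At a latent ICC of 0.05 part of the excess rejection comes from a small shift in the marginal log odds ratio (mean 0.06), so the SE ratio is the cleaner measure.

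**The case against.** **The size is unknown.** The article gives no ES ICC and only a minimum number of ES. A reader might infer that the interval is too narrow as a matter of fact. The article does not support that: the effect is nil at ICC 0, small to modest at 0.01 to 0.02, and substantial only near 0.05 with few ES. This stands, and the conclusion is conditional on it.

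**The SAP may deal with it.** The article defers to a committee-approved SAP that is not shown, and provider-level terms are often specified there. This limits the point but does not dispose of it, because the article itself fixes the clustering adjustment and names site alone.

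**Site might seem to enter twice.** Site is a stratification variable, so a literal reading has it both as a covariate and as the random intercept. The sentence can equally mean that site is handled through the intercept. Even on the literal reading, the duplication is redundant (fixed site effects drive the intercept variance to about zero) and does not narrow the interval for IPS. It calls for clearer wording and nothing more.

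**The sample size might seem too small.** It is not, for this reason: pooled power for 18 points hardly moves.

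**The data may not allow the fix.** The Local Data Collection System records "scheduled and attended IPS support sessions", but the article does not list ES identity as a field or say that a participant keeps one ES. This stands and has to be checked.

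**Conclusion.** The point holds in conditional form. The stated primary model has no term for ES, although ES are nested in the IPS arm only. If results differ between ES within a site, the confidence interval for the IPS effect will be too narrow and the primary test will reject too often. Over the assumed range the model SE is 4% to 27% too small and type I error is about 5.8% to 13.5%. A middle case of 20 ES and ICC 0.02 gives 10% and 7.3%. These figures rest on 416 participants per arm, equal caseloads, and assumed ES numbers and ICCs. The direction follows from the design; the size does not. The change is worth making because it is cheap and can be settled before the SAP is published. It does not call the design or the 832 into question.

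**What to change.** In the SAP:

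- Specify a partially nested logistic model with an ES random effect that applies to the IPS arm only and a small-sample correction for the number of ES. Make it the primary model, or at least a pre-specified sensitivity analysis reported beside the primary result.
- Define a participant's ES as the specialist first assigned after randomisation, so that the grouping does not depend on attendance or later changes of staff.
- Confirm that the Local Data Collection System captures an ES identifier with the session records. If it does not, add one while recruitment is still open.
- State that site enters once, either as fixed effects or as the random intercept.
- Report the estimated between-ES variance.

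The cost is SAP wording, one identifier and a somewhat wider interval; there is ample pooled power to bear it. The random effect may be poorly estimated with few ES. ES-clustered robust standard errors, with each TAU participant as a cluster of one, are a possible fallback, but a weak one with about 14 ES.
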